## Methods

### Study Design

#### Summary

This study is a parallel randomized controlled study (trial registration: KCT0006859) involving children aged 7-12 years diagnosed with ASD who volunteered to participate in the study with the consent of a legal guardian. The study will include an intervention group and a control group at a 1:1 ratio. Participants will be publicly recruited through the internet to enroll in a clinical trial through the Korean-Wechsler Intelligence Scale for Children-IV (K-WISC-IV) test administered by a professional clinical psychologist. Following neuropsychological evaluation, the children eligible for this study will be assigned randomly to the intervention or the control group for 4 weeks. Randomization will be performed using the PROC PLAN method in the SAS software program (version 9.4, SAS Institute). In this study, we plan to develop and apply a social skills training program for children with high-function ASD that can be implemented within the metaverse platform based on the PEERS program using digital technology. The PEERS is a social skills training program developed for children with ASD who face difficulties in making or retaining friends. The PEERS program has 14 sessions. The 1st session gives the introduction and trading information; the 2nd session is about conversational skills; the 3rd session is on electronic communication; the 4th session is about choosing appropriate friends; the 5th session is regarding the appropriate use of humor; the 6th session is about peer entry strategies; the 7th session is regarding peer exit strategies; the 8th session is about get togethers, the 9th is on good sportsmanship; the 10th is about handling teasing; the 11th is on handling bullying and bad reputations; the 12th is regarding arguments and disagreements; the 13th is about handling rumors and gossip; and the 14th one includes a graduation party and ceremony [12]. Under the guidance of a clinical psychologist (with a PhD in education) and a clinical specialist in psychiatry, “Becoming a Good Sportsman,” which is part of the PEERS program, was selected and conducted as a proof-of-concept study. Socializing with peers is important for children and adolescents with ASD to build close friendships and engage in positive peer interactions. To reduce the burden of discussing a wide range of topics, it is better to proceed with activities that go well together. “Becoming a Good Sportsman” was selected because experts considered it suitable for a test study because it is composed of activity-based socializing to become a good sportsman, which corresponds to the ninth session selected in our study [26]. To maintain the consistency of the program, a professional clinical psychologist trained during the study period will conduct it. To verify the effectiveness of the program, the results of neuropsychological evaluation, including social development indicators and biometric information (heart rate, heart rate variability, saturation, respiratory rate, and stress index), will be collected through wearable devices. Children enrolled in the study will be randomized into 2 groups with the same baseline characteristics. To verify the effectiveness of the program, for each group, first the differences between the neuropsychological evaluation results, including the social development index determined before the experiment and the test results after the experiment, will be compared and analyzed using a statistical method. Second, the differences in the neurophysiological scores between the groups will be compared and analyzed. Based on the results of these 2 processes, the effectiveness of the metaverse-based social skills training program using digital technology will be verified.

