#### Screening and Inclusion Criteria

We will recruit 24 children between March 2022 through treatment centers or internet-based social networking services. Inclusion criteria for children are the following: (1) age between 7 and 12 years, (2) diagnosed with ASD, (3) sufficient cognitive abilities to understand the rules with IQ≥90 according to a standardized intelligence test, (4) children and parents fluent in Korean, and (5) no defects in motor function. Written informed consent will be obtained from all the children and parents who will participate in this study.

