#### Sample Size

The sample size calculation provided by the clinical trial pilot test was employed because no studies were undertaken in advance to determine the effectiveness of the peer program by conducting exploratory clinical trials [38]. The recommended sample size for such pilot studies is 12 persons per group.

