#### Randomization and Masking

Participants will be assigned (1:1) to either the experimental or control group using permuted blocks (block size 4) and stratified by age (children aged 7-9 years and 10-12 years). An independent statistician will build the randomization list with consecutive subject numbers using the PROC PLAN method in SAS version 9.4.

Researchers providing the interventions are not blind; however, those who perform the neuropsychological assessments of the participants are blinded. Because all participants will receive the same outcome measures, assessors will not be able to identify which group a participant belongs to, based on the results. Wherever possible, if an assessor becomes unblinded, further evaluations for that participant will be completed by a different assessor (blind to the arm allocation).

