### Statistical Analysis

All baseline variables will be summarized in a randomized group. Continuous data will be reported as means (SD) unless skewed and will be reported as medians (IQR). Before testing the effectiveness of the program, an independent sample *t* test and a Mann-Whitney U test will be performed to determine whether there are differences in demographic variables between the groups. To compare the effects of all outcomes, the analysis will be conducted using the paired *t* test and Wilcoxon signed rank test. To evaluate treatment effects in each group, ANOVA will be repeatedly performed for determining differences in variables between the baseline and posttest for the treatment and control groups, with a condition analysis using (treatment vs control) × time (baseline vs posttest). ANOVA will be performed to compare the effects of the program between the groups and to determine whether there is a significant difference between each group by judging the rejection range based on a significance level of 0.05. We plan to perform statistical analysis using Python (version 3.8.5) and R (version 4.0.4).

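### The between-group test is a change-score comparison that adjusts for neither baseline nor the age stratum, and its deciding term is unclear; ANCOVA would usually be modestly more precise

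*Protocol article*

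**What the plan says.** All of this is in the Methods of the protocol article.

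- **Statistical Analysis, model.** Repeated ANOVA is planned on baseline and posttest, "with a condition analysis using (treatment vs control) × time (baseline vs posttest". A further sentence says that "ANOVA will be performed to compare the effects of the program between the groups" and that significance between the groups is judged at 0.05. No baseline covariate is named, and no term of the ANOVA is singled out as the treatment test.
- **Randomization and Masking.** Allocation is made "using permuted blocks (block size 4) and stratified by age (children aged 7-9 years and 10-12 years". The age stratum does not reappear in the analysis text.
- **Statistical Analysis, baseline.** t and Mann-Whitney tests are to be run before the effectiveness tests "to determine whether there are differences in demographic variables between the groups". Descriptive baseline summaries are planned as well.
- **Size.** "We will recruit 24 children between March 2022" and "The recommended sample size for such pilot studies is 12 persons per group". The Summary under Study Design gives a 1:1 ratio.
- **Data available.** Under Neuropsychological Test, the sociability measures are taken before and after the study. Table 1 places these assessments in weeks 1 and 6.

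**The concern.** With two groups and two time points, the group by time interaction is the same test as a t test comparing mean change between groups. A change score subtracts the whole baseline value, whatever the correlation between baseline and posttest. When that correlation is below 1 and the variances are similar, this over-corrects for chance baseline differences. ANCOVA estimates how much to subtract, and so usually has the smaller variance.

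The number of children is fixed at 24 by a pilot rule, so the choice of analysis is the available lever on precision. Both covariates will already be in hand: the baseline score from the pre-test and the age stratum from randomization.

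The wording adds a second problem. The sentence on significance between the groups can be read as referring to the interaction, to a posttest-only comparison, or to the group main effect. These are different tests with different power. The main effect averages a pre-treatment score, which the program cannot have affected, with the posttest, so it estimates half the effect.

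**Working it through.** **The plan's own figure.** 2 × 12 = 24, which agrees with the stated total. The article gives no effect size, SD or power, so there is no power calculation to reproduce.

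**Inputs.** From the article: 12 per group, 1:1, one baseline and one posttest, significance level 0.05. Assumed: two-sided test, true effect 0.8 SD on the posttest, equal pre and post variance (set to 1), pre-post correlation r from 0.3 to 0.95.

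**Variance factors for the treatment estimate** (each multiplied by 2/12)

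- Change score (the planned interaction): 2(1 − r), 22 df.
- ANCOVA on baseline: (1 − r²) × (1 + 1/(24 − 4)) = 1.05(1 − r²), 21 df. The factor 1.05 is the small-sample price of chance baseline imbalance when the slope is estimated.
- Large-sample ratio, ANCOVA to change score: (1 + r)/2. At N = 24 it is 1.05(1 + r)/2.

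Example at r = 0.7: change 2 × 0.3 = 0.60; ANCOVA 1.05 × 0.51 = 0.5355; ratio 0.89. The noncentrality is 0.8/√(0.60/6) = 2.53 for change and 0.8/√(0.5355/6) = 2.68 for ANCOVA. The noncentral t then gives 68% and 72%.

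| r | Change factor | ANCOVA factor | Ratio | Power, change | Power, ANCOVA | 24 × change/ANCOVA |
|---|---|---|---|---|---|---|
| 0.3 | 1.40 | 0.956 | 0.68 | 35% | 48% | 35 |
| 0.5 | 1.00 | 0.788 | 0.79 | 47% | 56% | 30 |
| 0.7 | 0.60 | 0.536 | 0.89 | 68% | 72% | 27 |
| 0.8 | 0.40 | 0.378 | 0.945 | 84% | 86% | 25 |
| 0.9 | 0.20 | 0.200 | 1.00 | 99% | 99% | 24 |
| 0.95 | 0.10 | 0.102 | 1.02 | about 100% | about 100% | 23 |

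The last column is the number of children the change-score analysis would need to match ANCOVA with 24. Adding the stratum takes ANCOVA from 21 to 20 df. Recomputing with 20 df lowers power by about 0.2 percentage points (72.4% to 72.2% at r = 0.7).

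**Other readings of the wording.** A posttest-only comparison has variance factor 1 and power 47% at every r. That equals the interaction at r = 0.5, exceeds it below 0.5 and falls short of it above. The group main effect has effect 0.8/2 = 0.4 and SD √((1 + r)/2). At r = 0.7 the SD is 0.92 and power is 17%, against 68% for the interaction.

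**Age stratum.** A simulation used 5,000 runs per setting, two strata of 12 and blocks of 4.

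- If age shifts pre and post scores equally (0.5 SD), adding the stratum to ANCOVA does nothing material: 55% without, 56% with, at r = 0.5.
- If age also shifts the change by 0.5 SD, adding it raises ANCOVA power from 49% to 56% (r = 0.5) and from 66% to 73% (r = 0.7).
- In that second setting, the change-score test without the stratum is conservative: type I error 4.6%, 4.1% and 2.5% at r = 0.5, 0.7 and 0.9, against about 5% with it.

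**The case against.** The strongest reply is that nothing here is an error. The interaction test is valid and unbiased under randomization, and baseline is used, as the first level of time. The trial is a self-described pilot with no power claim to undermine. All of that stands: this is a point about efficiency and clarity.

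The gain may also be small. The article gives no pre-post correlation. The two assessments are about five weeks apart, and the SRS-2 is described as rating the past 6 months, so a high correlation is plausible. At 0.8 the gain is two percentage points, and at 0.9 it has gone. A reader might infer that ANCOVA always gives the narrowest interval; the r = 0.95 row shows that it does not in a trial of this size.

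A reader might also take the 17% or 47% power as the cost of omitting ANCOVA. The text does not support that. It writes out condition by time and speaks of comparing the program's effects between groups, which points to the interaction. The lower figures only show why the deciding term should be named.

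The stratum is the weaker half. A condensed article may leave such a term to a fuller plan, a constant age effect cancels in change scores, and omission does not bias the estimate. The baseline tests cover demographic variables only and trigger no action, so they are a minor matter of reporting.

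What remains is that the between-group model is stated, not left open, and a usually better one is available from data already collected.

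**Conclusion.** The point holds as a moderate recommendation. The planned interaction is a valid change-score test. At N = 24, ANCOVA on baseline has 0.68, 0.79, 0.89 and 0.945 times its variance at r = 0.3, 0.5, 0.7 and 0.8, and no advantage from about 0.9 upward. In power this is a gain of 13, 9, 4 and 2 percentage points, under an assumed effect of 0.8 SD, equal variances and a two-sided 5% level. None of these assumptions, nor r, comes from the article.

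The age stratum adds precision only if age predicts the change, or the posttest given baseline. The ambiguity about the deciding term needs correcting whatever r is: at r of 0.7 or more both alternative readings have lower power than the interaction, and the group main effect estimates half the effect at any r. The documents do not support calling the plan invalid or biased.

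**What to change.** Replace the ANOVA sentences with one between-group analysis, for example:

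> For each outcome, the posttest score will be analysed by ANCOVA with treatment group, the baseline value of the same score and age stratum (7-9 / 10-12 years) as terms. The treatment coefficient with its 95% CI is the estimate of effect.

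Delete the baseline t and Mann-Whitney tests and keep the descriptive summaries by group that are already planned.

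The cost is wording and two degrees of freedom (22 to 20). No new data are needed, because baseline scores and age are already collected.

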
#### Neuropsychological Test

To confirm that the children who wished to participate in the study meet the research criteria, the K-WISC-IV test, an intelligence test that comprehensively evaluates the overall intellectual ability of children, will be performed before the start of the study [27]. To compare and evaluate the effectiveness of the metaverse-based social skills training program developed in this study, a series of neuropsychological tests will be performed before and after the study to evaluate sociability. Neuropsychological tests to be used in the study include the Social Responsiveness Scale (SRS), evaluated by parents, as a tool to verify the effectiveness of children's social interactions. Furthermore, the Korean version of the Child Behavior Checklist (K-CBCL) and the Korean version of the Vineland Adaptive Behavior Scale-2 (K-VABS-2) test are used as evaluation tools to verify the children's overall problematic behavior, adaptability, and sociability-related effects as determined through a parental survey. The Children’s Depression Inventory (CDI) and revised Children’s Manifest Anxiety Scale (RCMAS) are used as assessment tools to compare mental health levels, such as stress relief, depression, and anxiety before and after intervention.

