5	Being a Good Sportsman 4 (internet): knowing and accepting individual differences	To be able to recognize the characteristics of other team members and accept similarities and differences with friends while working as a team	Greeting therapists and participants Checking the homework from the last session Educating and practicing “knowing and accepting” skills. Playing sports games in metaverse Giving session feedback
6	Neuropsychological test (offline)	Conducting postneuropsychological evaluation	Postneuropsychologital evaluation: K-SCQ^a^ SRS 2^b^ K-CBCL^c^ K-VABS-2^d^ SCL-R^e^ CDI^f^ RCMAS^g^

^a^K-SCQ: Korean Version of the Social Communication Questionnaire.

^b^SRS-2: Social Responsiveness Scale-2

^c^K-CBCL: Korean version of the Child Behavior Checklist.

^d^K-VABS-2: Korean version of the Vineland Adaptive Behavior Scale-2.

^e^SCL-R: Symptom Checklist-Revision.

^f^CDI: Children’s Depression Inventory.

^g^RCMAS: revised Children’s Manifest Anxiety Scale

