#### Social Responsiveness Scale-2 (SRS-2)

The SRS-2 is an evaluation tool used to verify the effectiveness of social interactions. This test is a questionnaire that asks parents or teachers to evaluate the characteristics of social interactions that children have displayed in the past 6 months and consists of 65 items. Each question is rated from “not at all” (0 points) to “almost always” (3 points) and can be scored on a scale of 0-195 points. The evaluation content consists of social insight, social information processing, mutual social communication ability, social anxiety/avoidance, and autistic immersion and traits. Higher scores indicate lower social functioning [31].

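### No primary outcome is named and every outcome is tested at 0.05, so with five to seven scales the chance of at least one false-positive group difference is up to about 23% to 30%

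*Protocol article*

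**What the plan says.** All references are to the protocol article.

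- **Decision rule.** Statistical Analysis starts its treatment of effects with "To compare the effects of all outcomes, the analysis will be conducted using the paired" t test and the Wilcoxon signed rank test. It then adds a group-by-time ANOVA, and an ANOVA to decide whether "there is a significant difference between each group by judging the rejection range based on a significance level of 0.05". No other significance level appears, and no outcome is set apart.
- **Outcomes.** Neuropsychological Test names five scales with an evaluative role: SRS, K-CBCL, K-VABS-2, CDI and RCMAS. The week 6 row of Table 1 names seven: "K-SCQ^a^ SRS 2^b^ K-CBCL^c^ K-VABS-2^d^ SCL-R^e^ CDI^f^ RCMAS^g". Study Design (Summary) adds five biometric measures from the wearable device.
- **Closest wording to a primary outcome.** Neuropsychological Test describes the "Social Responsiveness Scale (SRS), evaluated by parents, as a tool to verify the effectiveness of children's social interactions", and the Measures section says "The SRS-2 is an evaluation tool used to verify the effectiveness of social interactions". K-CBCL and K-VABS-2 are described in parallel terms in both places.
- **Use of the results.** The second objective in the Introduction is to validate effectiveness. Study Design and Biometric Information both say that effectiveness will be verified.
- **Status.** Study Design calls the trial a proof of concept, and Limitations calls it a pilot. Sample Size gives 12 per group from a pilot-study recommendation.

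**The concern.** The article promises a verdict on effectiveness but does not say which result delivers it. Several scales are each judged at 0.05, and nothing says what follows if they disagree. The error rate attached to an effectiveness claim is therefore not the 5% that the stated level suggests. A reader of the results could not tell whether a significant scale was the one the trial set out to test or one of several that happened to cross the line.

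A multiplicity procedure might reasonably sit in an analysis plan that is not shown. The choice of the outcome that decides the trial is different: it belongs in the protocol. The article describes every instrument at length without making that choice.

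**Working it through.** **Inputs from the article.** Level 0.05 per test (Statistical Analysis); five scales (Neuropsychological Test) or seven instruments (Table 1, week 6); five biometric measures (Study Design); 12 per group, allocated 1:1 (Sample Size; Randomization and Masking). The article states no family-wise error rate, so there is no figure of its own to reproduce.

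**Assumptions.** Tests are two-sided (sidedness is not stated), each instrument contributes one total score tested once between groups, and there is no true effect on any of them. The correlations between scales are assumed. With two groups and two time points, the group-by-time test is equivalent to a two-sample t test on change scores, so two-sample t tests are used below.

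**Independent tests.** The chance of at least one false positive among k tests is 1 − 0.95^k. The chance of at least one in the favourable direction is 1 − 0.975^k.

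| Tests | Any direction | Favourable only |
|---|---|---|
| k = 5 | 1 − 0.95^5 = 0.226 | 1 − 0.975^5 = 0.119 |
| k = 7 | 1 − 0.95^7 = 0.302 | 1 − 0.975^7 = 0.162 |

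**Correlated tests.** Simulated two-sample t tests, 12 per group, k = 7, 20,000 runs, with the same correlation between every pair of outcomes:

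| Assumed correlation | Any direction | Favourable only |
|---|---|---|
| 0 | 0.302 | 0.162 |
| 0.3 | 0.271 | 0.136 |
| 0.5 | 0.234 | 0.120 |
| 0.7 | 0.181 | 0.091 |

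For the seven totals the risk is thus about 18% to 30%, or 9% to 16% in the direction that would support the program.

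**If more were tested.** Adding the five biometric measures gives k = 12: 1 − 0.95^12 = 0.460 if independent, and 0.327 by simulation at correlation 0.5. Under independence the any-direction risk first passes one half at k = 14 (1 − 0.95^14 = 0.512). The article does not say that subscales will be tested, nor how the biometric measures enter the group comparison, so the k = 12 figure is illustrative. The within-group paired tests are a further route to a claim and are not counted here.

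**Cost of the alternatives.** One primary outcome at 0.05 keeps the error of the effectiveness claim at 5%. Keeping all seven confirmatory with Bonferroni means 0.05/7 = 0.0071 per test. At 12 per group and 80% power, the detectable difference then rises from about 1.20 SD to about 1.57 SD.

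**The case against.** The strongest reply is that this is a small proof-of-concept trial. It is sized by a pilot rule, it disclaims generalization, and any multiplicity method may be in an analysis plan that is not shown. Seven is also a generous count: the Measures section presents the K-SCQ as a screening tool and gives the SCL-R no role in judging effectiveness. On the five remaining scales the ceiling is nearer 23%, and only about half of that is in the favourable direction. Nor does the article state that one significant scale suffices. Study Design bases its conclusion on two steps taken together, change within each group and differences between groups.

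Much of this stands and lowers the severity. It does not remove the point. The Limitations section covers generalization and long-term effect, not multiple testing. The pilot label also sits beside a promise to verify effectiveness, and the two-step description does not say which scale the steps apply to.

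A reader might also infer that the K-SCQ and SCL-R have no baseline, because Table 1 names them only at week 6. The text does not show this. The week 1 row mentions a pre-test evaluation without naming any instrument, so all seven, SRS-2 included, are itemized only at week 6. The list under Neuropsychological Test is also worded as non-exhaustive: "Neuropsychological tests to be used in the study include the Social Responsiveness Scale (SRS), evaluated by parents". The two lists differ and should be reconciled, but a missing baseline is not established.

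**Conclusion.** The point holds. No primary outcome is named, all outcomes are judged at 0.05, and the results are meant to verify effectiveness. With no true effect, the chance of at least one false-positive between-group result is up to about 23% (five scales) or 30% (seven instruments) if the tests are independent. For seven it is about 18% to 30% over assumed correlations from 0.7 to 0, and about 9% to 16% in the favourable direction. These figures rest on two-sided tests and one total score per instrument.

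Three stronger readings are not supported:

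- **That a false claim is likely.** This would need many weakly correlated subscales to be tested as well. The article describes subscales but does not say they will be tested.
- **That most significant results would be chance findings.** That share depends on power and on how many true effects exist. The calculation above assumes none, so it cannot show it.
- **That the SRS-2 is already the primary outcome.** Its wording is closest to the objective, but K-CBCL and K-VABS-2 are given parallel wording.

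Given the pilot status, this should be fixed but is not a critical flaw.

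**What to change.** 1. Before data are seen, name one primary outcome and one contrast. The best-supported candidate is the SRS-2 total score, compared between groups at post-test and tested at 0.05. The article dates the study to March to May 2022 and its own publication to June 2022, so record when the choice was made.
2. State the limits of that choice. Parents rate the scale in a trial whose control group receives no intervention, so blinding the assessors does not protect it. The SRS-2 entry under Measures gives a reference period of the past 6 months, which must be reconciled with a post-test in week 6.
3. Label all other scales and the biometric measures exploratory. Report estimates with 95% confidence intervals and draw no effectiveness claim from them.
4. Reconcile the test lists in Neuropsychological Test and Table 1, so that it is clear which instruments are given at pre-test and which at post-test.

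The cost is about a paragraph of text, and the sponsor gives up claiming effectiveness from a non-primary scale. That is cheaper than a seven-way Bonferroni correction, which a trial with 12 per group can ill afford.
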